***(1) Phase 1: To identify possible CEBA profiles among PwMS***	
To achieve this objective, it will be investigated (1a) which proportion of the PwMS present with which CEBA symptoms, (1b) if PwMS and healthy controls differ on scores on neuropsychological tests and questionnaires regarding the CEBA domains, and if so, on which domain(s) they differ, (1c) which CEBA profiles (i.e., clustering of CEBA symptoms) exist among PwMS, (1d) if CEBA symptoms of PwMS are stable over time, (1e) how the identified CEBA profiles relate with demographic and disease related characteristics, and (1f) to what extent societal participation of PwMS can be predicted by the identified CEBA profiles and/or CEBA symptoms	

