## Methods

### Study design

The MS-CEBA study is an observational, prospective, cohort study consisting of three phases, as outlined in Table 1. The study aims to include a group of 300 PwMS in Phase 1, of whom 54 will undergo retesting after one year to investigate the stability of the results. Additionally, a group of 100 healthy controls (HCs) will be included in Phase 1. After two years, a second group of 100 PwMS will be included in Phase 2 to investigate whether the results of Phase 1 can be replicated, thereby validating the CEBA profiles. A neuropsychological screening instrument for timely identification of CEBA profiles will then be developed. In Phase 3, a qualitative evaluation of a small group of PwMS (n = 10) from Phase 2 who sought neuropsychological rehabilitation treatment using the advice obtained with the screening instrument (as a part of clinical care, not an intervention in this study) will be performed to identify whether and how this treatment adequately matched their expectations. If necessary, suggestions for adjustments to, or combining of, existing neuropsychological treatments in future research will be made based on this evaluation.

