### Study procedures

#### Phase 1: Identification of possible CEBA profiles

Data collection and management of the 300 PwMS will be performed by the researchers (neuropsychologists). When informed consent is received, PwMS will be approached by the researcher to schedule the NPA. Prior to the NPA, PwMS will receive questionnaires regarding fatigue, mood, behaviour and societal participation to fill out at home (Table 2). The questionnaires will be sent digitally via the secure web app Research Electronic Data Capture (REDCap) [48, 49] or, upon request, on paper.

**Table 2 Tab2:** Overview of the assessments used in the MS-CEBA study

Assessment	Construct	Phase 1 PwMS^a^ *(n* = 300)	Phase 1 HCs^b^ (*n* = 100)	Phase 1 Retest PwMS (n = 54)	Phase 2 PwMS (*n* = 100)

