**Neuropsychological assessment (participants)**					
Symbol Digit Modalities Test (SDMT)	Information processing speed (Cognition)	✓	✓	✓	✓
15 Words Test (15-WT)	Verbal memory (Cognition)	✓	✓	✓	✓
Digit Span Test of the Wechsler Adult Intelligence Scale (WAIS) IV	Memory span/working memory (Cognition)	✓	✓	✓	✓
Trail Making Test (TMT)	Attentive/executive functioning (Cognition)	✓	✓	✓	✓
Letterfluency Test (LFT)	Attentive/executive functioning (Cognition)	✓	✓	✓	✓
Facial Expressions of Emotion: Stimuli and Tests (FEEST)	Social cognition (Behaviour)	✓	✓	✓	✓
^a^PwMS: People with Multiple Sclerosis; ^b^HCs: Healthy Controls; ^c^EDSS: Expanded Disability Status Scale; ^d^MS: Multiple Sclerosis					

Upon registration for participation, PwMS are asked to provide contact information about a proxy (e.g., significant other or other close relative). Informed consent for the proxy will also be obtained before study participation. The proxy is asked to fill out two questionnaires prior to the NPA appointment, either digitally via REDCap [48, 49] or on paper (Table 2). The proxy does not have to attend the NPA appointment.

The NPA takes approximately 90 minutes and consists of an anamnesis regarding demographic and disease characteristics, sleep, coping style, subjective complaints and highest experienced burden, and a neuropsychological test battery concerning different cognitive domains, including social cognition (Table 2). For the retest of Phase 1, PwMS who at administration for participation gave consent to be approached for possible follow-up research, will be asked to participate in the retest sample, after approximately one year.

From the group of 100 HCs, informed consent will be obtained before study participation as well. The questionnaires and test battery of the NPA will be the same as for the PwMS, but parts of the anamnesis (concerning disease characteristics, subjective complaints, and highest experienced burden), as well as proxy measures, will be excluded.

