### Statistical analysis

For analysing the data, Statistical Package for the Social Sciences (SPSS) version 28.0 and/or R, possibly combined with Latent GOLD version 6.0 [50], depending on the availability of suitable packages in R, will be used. For all analyses, the nominal significance level will be set at α = 0.05, 2 sided. The numbering of the analyses described below corresponds to the numbering of the objectives displayed in Table 1*.* In the following, T0 refers to the first group of 300 PwMS, and T1 refers to the retesting of 54 PwMS.

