**Phase 1: Identification of possible CEBA profiles.** 1a) Summary statistics will be computed, describing percentages of PwMS (n = 300) with CEBA symptoms, based on scores on the neuropsychological tests and questionnaires regarding each CEBA domain; 1b) MANOVAs with follow-up ANOVAs will be computed comparing PwMS *(n* = 300) to HCs (*n* = 100) on scores on the neuropsychological tests and questionnaires regarding the Cognitive and Behavioural domain, and ANOVAs will be computed comparing PwMS to HCs on scores on questionnaires regarding the Energetic and Affective domain; for 1c) and 1e) a three-step mixture analysis will be computed [51]: step 1 is a latent profile analysis to identify clusters of PwMS with common CEBA profiles; step 2 is to estimate the posterior cluster membership probabilities of the model from step 1 for each PwMS in the sample, and step 3 is to relate the cluster membership probabilities from step 2 to relevant predictors, i.e., a regression analysis will be carried out to estimate the relationship between the CEBA profiles and the demographic and disease-related variables, with an adaptation to account for the fact that cluster membership is estimated, rather than observed; for 1d) repeated measures MANOVAs will be computed comparing T1 (n = 54) to T0 (n = 300) on the scores on neuropsychological tests and questionnaires for the Cognitive and Behavioural domain separately; if a time effect is indicated, these will be followed by post hoc analyses (repeated measures ANOVAs), to assess which variable(s) the time effect pertains to. A repeated measures ANOVA will be computed comparing T1 to T0 on the scores on questionnaires regarding the Energetic and Affective domain separately; 1f) regression analysis will be carried out, considering two competing models: model 1, using the membership of the CEBA profiles as a predictor; and model 2, using the most distinguishing outcome variables (scores on neuropsychological tests and questionnaires in each of the CEBA domains) as predictors.

**Phase 2: Validation of CEBA profiles and development of the CEBA screening instrument.** 2a) The posterior cluster membership probabilities of the selected latent profile model from Phase 1 will be estimated for each of the PwMS in the new sample (n = 100). The equality of the distributions of membership probabilities of the new sample and Phase 1 sample will be tested using a chi-square test. 

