### Sample size

The sample size calculations provided below were performed following *G*Power* [52]. Since for objective 2b and objectives 3a and 3b (Table 1), no statistical analyses will be carried out, a sample size calculation is not relevant for these objectives.

With regard to objectives 1a and 1c, here, the main study parameter is the CEBA profile, which is latent and thus needs to be derived from performance on neuropsychological tests and questionnaires regarding the CEBA domains. For identification of the CEBA profiles, latent profile analysis will be performed. A minimum sample size of 300 is suggested for latent profile analysis to ensure that there is sufficient power to estimate all model parameters and recover the true number of classes [53, 54]. Therefore, the aim is to include a minimum of 300 patients. For objective 1b, the main study parameters are possible differences between PwMS and HCs on neuropsychological tests and questionnaires regarding symptoms in the different CEBA domains, which will be investigated through the performance of MANOVAs and ANOVAs. A power calculation (with a medium effect size [Cohen’s f] = 0.5, α = 0.05, power = 0.95) results in a minimal sample size of n = 60, which is expected to be exceeded with our goal of including 300 PwMS and 100 HCs for comparison of performance in the CEBA domains. With regard to objective 1d, here, the main study parameters are possible differences in CEBA symptoms between T0 and T1, which are derived from scores on neuropsychological tests and questionnaires regarding the CEBA domains. To investigate the extent to which individual CEBA symptoms are stable over time, repeated measures MANOVAs and ANOVAs will be performed to compare T0 to T1. Within-between interactions will be used. Here, a power calculation using repeated measure analysis (with medium effect size Cohen’s f = 0.5, α = 0.05, and power = 0.95) results in a total sample size of n = 54. Therefore, the aim is to include a minimum of 54 patients for comparing T0 to T1. Since objectives 1e and 1f, as well as objective 2a, depend on the CEBA profiles yet to be identified, the corresponding analyses are considered exploratory, and therefore, no sample size calculation will be provided at this stage. At a later stage, after the CEBA profiles have been identified, sample size calculations for these objectives will be provided, again using *G*Power* [52].

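### The one-year stability analysis (1d) has no retested controls, so on the six performance tests the time effect cannot separate symptom change from any gain due to earlier testing.

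*Protocol article*

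**What the plan says.** Table 1 of the protocol article sets objective 1d: to find out "if CEBA symptoms of PwMS are stable over time". Study design takes the retest sample from the 300 Phase 1 patients, "of whom 54 will undergo retesting after one year to investigate the stability of the results". Statistical analysis defines the second occasion in the same way: "T1 refers to the retesting of 54 PwMS".

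Table 2 lists the same six performance instruments at Phase 1 and at retest: SDMT, 15-WT, Digit Span, TMT, LFT and FEEST. Its only retest column is headed "Phase 1 Retest PwMS (n = 54)". The 100 healthy controls have a single Phase 1 column. The text below the table says that consenting patients "will be asked to participate in the retest sample, after approximately one year".

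The analysis is repeated measures MANOVA for the Cognitive and Behavioural domains, "comparing T1 (n = 54) to T0 (n = 300) on the scores on neuropsychological tests and questionnaires", and repeated measures ANOVA for the Energetic and Affective domains. The trigger for follow-up is a time effect: "if a time effect is indicated, these will be followed by post hoc analyses (repeated measures ANOVAs), to assess which variable(s) the time effect" concerns. Sample size names the quantity of interest for 1d as "possible differences in CEBA symptoms between T0 and T1". It adds that an interaction of a within-subject with a between-subject factor will be used, but names no between-subject factor.

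**The concern.** A performance test taken twice can yield a better second score because the person has met the task before. If that happens, the mean difference between T1 and T0 in patients has two parts:

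observed mean change = true symptom change + retest gain.

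A retested comparison group would give an estimate of the second part. Here no one outside the patient group has a T1 score, so the data supply only the sum, while the plan labels that sum a difference in symptoms.

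The error can go either way. Stable patients with some retest gain may show a time effect that is read as symptom change. Patients who decline by about as much as they gain from practice may show none and be read as stable.

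Self- and proxy-report questionnaires (HADS, DMFS, DEX, behavioural changes) carry no performance gain of this kind. A stability result therefore does not mean the same thing in every domain. In the Behavioural MANOVA the two kinds of measure sit together: FEEST alongside the questionnaires.

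**Working it through.** **The plan's own figure.** Sample size gives n = 54 for 1d from f = 0.5, alpha 0.05 and power 0.95. With the usual repeated measures formula, noncentrality = f² × N × m / (1 − rho), two occasions (m = 2), and two groups and rho = 0.5 assumed because they are not stated:

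- f = 0.5 gives N = 16 (noncentrality 0.25 × 16 × 2 / 0.5 = 16).
- f = 0.25 gives N = 54 (noncentrality 0.0625 × 54 × 2 / 0.5 = 13.5; power 0.950).
- A paired t test with a standardised mean change of 0.5 also gives 54 (power 0.950).

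So 54 does not follow from the stated f under these assumptions. It does fit a paired test of mean change. That is a separate matter and nothing below depends on it.

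**Inputs for the check.** From the protocol: n = 54 pairs, two-sided alpha 0.05, patients only. Not in the protocol, hence assumed: a practice gain g of 0 to 0.3 of the T0 SD, and a retest correlation r of 0.5, 0.7 or 0.8. Equal SDs at both occasions are also assumed.

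**Formula, single test.** In T0 SD units the change score has SD √(2(1 − r)), which is 1.000, 0.775 and 0.632 for the three values of r. With 53 degrees of freedom the critical value is 2.006. The test statistic is noncentral t with

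ncp = √54 × (g − true decline) / √(2(1 − r)).

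Example: g = 0.2, no decline, r = 0.7 gives 7.348 × 0.2 / 0.775 = 1.90, and a rejection probability of 0.46.

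**Probability of a time effect when symptoms have not changed**

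| Assumed gain (SD) | r = 0.5 | r = 0.7 | r = 0.8 |
|---|---|---|---|
| 0 | 0.05 | 0.05 | 0.05 |
| 0.05 | 0.065 | 0.075 | 0.088 |
| 0.1 | 0.11 | 0.15 | 0.21 |
| 0.2 | 0.30 | 0.46 | 0.63 |
| 0.3 | 0.58 | 0.80 | 0.93 |

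**Probability of detecting a true decline of 0.3 SD**

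| Assumed gain (SD) | r = 0.5 | r = 0.7 | r = 0.8 |
|---|---|---|---|
| 0 | 0.58 | 0.80 | 0.93 |
| 0.1 | 0.30 | 0.46 | 0.63 |
| 0.2 | 0.11 | 0.15 | 0.21 |
| 0.3 | 0.05 | 0.05 | 0.05 |

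**Cognitive MANOVA, illustration only.** Assume one score from each of the five cognitive tests, the same gain on each, and a common correlation between change scores. The test is then a one-sample Hotelling T² with noncentrality 54 × 5 × (g² / (2(1 − r))) / (1 + 4 × correlation). At a gain of 0.2 SD the rejection probability runs from 0.21 (r = 0.5, correlation 0.6) to 0.82 (r = 0.8, correlation 0.2). At 0.1 SD and r = 0.5 it is only 0.095 (correlation 0.4) or 0.083 (correlation 0.6). The article does not say how many scores each test contributes, so these figures carry less weight than the single-test ones.

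**The case against.** The strongest reply is that the premise comes from outside the documents. They mention no practice effect, and after about a year any gain may be small or gone. This stands as far as size is concerned. At zero gain the test keeps its level, and at 0.05 SD the excess is slight. A reader might infer that zero is the wrong null value, that stable patients should be expected to improve, or that the false-positive rate is always more than double alpha. The documents support none of these. What remains is that the design cannot tell the two components apart, whatever their size.

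Second, Table 2 lists instruments, not versions. A reader might infer that identical forms are repeated. The article does not say so, and a full protocol may well settle it, so silence on versions is not a fault here. Parallel forms might reduce a gain; they would not by themselves estimate it.

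Third, Sample size announces a within-by-between interaction for 1d. A contrast between patient subgroups would cancel a gain they share, but it would answer whether subgroups change differently, not whether symptoms are stable. Statistical analysis names no such factor for 1d, and controls cannot supply one without a T1 score. The normative and control data mentioned elsewhere are not described as retest data.

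Fourth, this is one of six Phase 1 sub-objectives and no decision rule hangs on it. That stands. A reader might infer that 1d underpins the choice of treatment. The article does not say so: it bases treatment advice on profile and highest experienced burden.

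**Conclusion.** The point holds for the six performance tests and for the interpretation of 1d only. The article fixes a patients-only retest, a time effect as the criterion and a reading of that effect as symptom difference. Together these leave symptom change and retest gain inseparable. An analysis plan that is not shown could add an adjustment, but it could not create control data at T1.

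The size is unknown. Over assumed gains of 0 to 0.3 SD and r = 0.5 to 0.8, the chance that a single test shows a time effect without symptom change runs from 0.05 to 0.93. At r = 0.7, the chance of detecting a true 0.3 SD decline falls from 0.80 with no gain to 0.15 with a 0.2 SD gain. The primary outcome, the latent profiles from Phase 1, is not touched, and neither is the questionnaire part of 1d. The point is worth correcting because it decides what 1d may conclude and the correction is cheap.

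**What to change.** In 1d:

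1. Analyse the six performance tests separately from the questionnaires. This takes FEEST out of the MANOVA that also holds the behavioural questionnaires.
2. For each performance test, report the mean paired change with its 95% CI, unadjusted and after subtracting a prespecified range of practice gain that starts at 0, for example 0 to 0.4 of the T0 SD. Where retest reference data exist for a test, use that gain as the main value.
3. State the gain at which the conclusion changes.
4. Describe the unadjusted time effect on these tests as symptom change plus practice, not as symptom change or stability.
5. Reconcile the interaction sentence in Sample size with the patients-only time effect in Statistical analysis: name the between-subject factor or remove the sentence.
6. Record the test version used at each occasion, and do not change versions partway through the retests. A switch would add a version difference to the time effect.

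This needs a few lines of wording and one extra table, with no new participants or visits. The price is a less definite stability conclusion for the Cognitive tests and FEEST. For scale, at r = 0.7 the 95% CI half-width is 2.006 × 0.775 / √54 = 0.21 SD, so a 0 to 0.4 SD range of assumed gain moves the estimate by more than its sampling error.

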### Objectives

The MS-CEBA study aims to identify possible different CEBA profiles and the relationships between such CEBA profiles and societal participation in PwMS. If different CEBA profiles can be established, the aim is to validate the CEBA profiles found in a new group of PwMS. If successful, our aim is to develop a compact neuropsychological screening instrument that is feasible for use in clinical practice and which allows the timely identification of specific CEBA profiles without putting an unnecessary load on PwMS. With this compact screening instrument, PwMS can be timely referred to the neuropsychological rehabilitation treatment most suitable for their specific CEBA profile. Subsequently, by means of a qualitative evaluation, it will be assessed whether this method of selecting treatment indeed proves effective and the selected treatment is suitable for the given CEBA profile or whether, in future research, the existing neuropsychological treatments should be adapted or combined to meet the needs of PwMS. All of this is done with the overarching aim to improve societal participation and quality of life of PwMS. These objectives and the associated subobjectives are presented in Table 1. The study will be divided into 3 phases, pertaining to [1] identification of the CEBA profiles, [2] validation of the profiles and development of the screening instrument, and [3] evaluation of the recommended neuropsychological rehabilitation treatment.

**Table 1 Tab1:** Objectives of the MS-CEBA study

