**Questionnaires (participants)**					
Hospital Anxiety and Depression Scale (HADS)	Anxiety and depression (Affect)	✓		✓	✓
Dutch Multifactor Fatigue Scale (DMFS)	Fatigue (Energy)	✓		✓	✓
Dysexecutive questionnaire (DEX)—self	Dysexecutive syndrome and behavioural changes (Behaviour)	✓		✓	✓
Impact on Participation and Autonomy questionnaire (IPA)	Participation	✓		✓	✓

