#### Secondary outcomes

Secondary outcomes are the relationships of the CEBA profile with demographic and disease-related characteristics, such as MS subtype, age of disease onset, medication and EDSS (obtained from anamnesis or medical records), and level of societal participation (derived from the score on the Impact on Participation and Autonomy (IPA) questionnaire), all of which are listed in Table 2.

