## Discussion

To the best of our knowledge, the MS-CEBA study is the first to investigate, over the whole spectrum of CEBA domains, whether there are symptoms in the different domains that consistently occur together in PwMS. In other words, if certain CEBA profiles can be identified, and in turn, how these possible profiles are related to the level of societal participation of PwMS. We believe that increased awareness of and knowledge on the combinations of neuropsychological problems in MS is a meaningful contribution to the literature and to neuropsychological rehabilitation care for PwMS for various reasons.

First, if specific CEBA profiles are indeed discovered, this is an important step in systematically mapping the neuropsychological symptoms that this heterogeneous patient group presents with. This allows for a more structured screening of these combinations of neuropsychological symptoms in PwMS by developing a time-efficient screening instrument taking into account all CEBA domains as well as the highest experienced burden. Standard deployment of the screening instrument in clinical practice, and thereby more consistent and timely attention to the combinations of neuropsychological symptoms of MS, will help prevent these combinations of symptoms from going unnoticed for an extended period of time. Therefore, in the future, PwMS who present with a given CEBA profile will be more timely and fully informed about the most suitable existing neuropsychological rehabilitation treatment options for their profile, and if desired, treatment can be started in a timely manner.

Second, the current dataset will enable the exploration of demographic and medical data as potential predictors for specific CEBA profiles and, additionally, how each corresponding CEBA profile relates to the level of societal participation. This provides insight into potential risk factors for certain CEBA profiles and the corresponding level of societal participation, contributing further to the timely identification of CEBA profiles and, associated with this, the timely indication for neuropsychological rehabilitation treatment in PwMS.

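### Objective 1f compares two data-derived models of participation with no independent check described, although the participation questionnaire is also collected in 100 new Phase 2 patients and enters no stated analysis there

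*Protocol article*

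**What the plan says.** Table 1 of the protocol article, objective 1f, asks "to what extent societal participation of PwMS can be predicted by the identified CEBA profiles and/or CEBA symptoms". The Objectives section words the same aim more softly, as "the relationships between such CEBA profiles and societal participation in PwMS".

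Under Statistical analysis, 1f reads: "regression analysis will be carried out, considering two competing models: model 1, using the membership of the CEBA profiles as a predictor". Model 2 is described as "using the most distinguishing outcome variables", meaning test and questionnaire scores from the CEBA domains. The text for 1f names no sample, time point or hold-out set.

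On timing, the Phase 1 study procedures say: "Prior to the NPA, PwMS will receive questionnaires regarding fatigue, mood, behaviour and societal participation to fill out at home". Table 2 ticks the IPA for the 300 Phase 1 patients, the 54 retested patients and the 100 Phase 2 patients. Phase 2 follows the same inclusion and assessment procedure as Phase 1.

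The Sample size section calls 1e, 1f and 2a exploratory and defers their sample sizes until the profiles are known.

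**The concern.** Objective 1f asks how well participation can be predicted, and it sets two models against each other. Both models are products of the Phase 1 data. The profiles in model 1 are estimated there, and the distinguishing scores in model 2 can be known only once those profiles exist. If R2 is then computed in the same patients, it overstates how well either model would do in new ones. The size of the overstatement depends on how many scores are used and how they were picked. The comparison could therefore turn partly on flexibility instead of on predictive value.

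The result also feeds the later argument of the article, where profiles inform timely indication for treatment. For that use, performance in patients who played no part in building the models is the relevant figure. Those patients will be assessed with the same instruments, yet no stated analysis uses their IPA.

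**Working it through.** **Step 1. Where the IPA is collected and where it is used.**

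| Set | n | IPA collected (Table 2) | Stated analysis | IPA used |
|---|---|---|---|---|
| Phase 1, T0 | 300 | yes | 1f, by natural reading | yes |
| One-year retest, T1 | 54 | yes | 1d: the four CEBA domains | no |
| Phase 2 | 100 | yes | 2a: distribution of profile membership | no |

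The article states that 2b and Phase 3 involve no statistical analysis. So 54 + 100 = 154 IPA assessments enter no stated analysis. That 1f uses T0 data is an inference: it is a Phase 1 objective, T0 is the sample of 300, and no lag is mentioned.

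**Step 2. Size of the in-sample optimism.** The article gives no figure for 1f, so there is none to reproduce. The size was simulated under assumptions that are not in the article: 15 candidate scores with mutual correlation 0.3, equal coefficients of 0, 0.05 or 0.10 and unit residual variance, four scores selected, least squares at n = 300, evaluation in 2,000 new observations, 1,000 datasets per scenario. R2 = 1 − (residual sum of squares) / (total sum of squares), with coefficients held fixed in the new observations.

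| Selection of the four scores | True relation | R2 in sample | R2 in new patients | Difference |
|---|---|---|---|---|
| by correlation with the IPA | none | 0.03 | −0.03 | 0.06 |
| by correlation with the IPA | weak | 0.18 | 0.11 | 0.07 |
| by correlation with the IPA | stronger | 0.39 | 0.31 | 0.08 |
| by separation of three groups, or blind | none | 0.014 | −0.018 | 0.03 |
| by separation of three groups | stronger | 0.34 | 0.31 | 0.03 |

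As a check on the fourth row, the expected in-sample R2 with four predictors and no relation is 4 / 299 = 0.013. Blind selection with a stronger relation gives about 0.02. Selection that never looks at the IPA therefore leaves little more than ordinary four-predictor overfitting, 0.02 to 0.03.

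**Step 3. What the unused data could support.** Assume f2 = 0.15, so R2 = 0.15 / 1.15 = 0.13, and 3 to 5 profiles (2 to 4 indicator variables). The overall F test of model 1, refitted, has noncentrality f2 × n at two-sided α = 0.05:

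- Phase 2, n = 100: 0.15 × 100 = 15, power 0.94, 0.91 and 0.87 for 2, 3 and 4 indicators.
- Retest, n = 54: 0.15 × 54 = 8.1, power 0.70, 0.62 and 0.56.
- With f2 = 0.02 instead, power is 0.22 to 0.17 at n = 100 and 0.13 to 0.10 at n = 54.

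Approximate 95% intervals for an observed R2 of 0.13, from tanh(atanh(√0.13) ± 1.96/√(n − 3)) squared, are 0.03 to 0.27 at n = 100 and 0.01 to 0.33 at n = 54. Phase 2 thus gives a usable external check if the relation is of medium size. The retest gives only an imprecise estimate.

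**The case against.** The strongest reply is that nothing here is an error. Predict is ordinary regression vocabulary, the aim is elsewhere called a relationship, and 1f is declared exploratory. The retest was sized for stability and Phase 2 is meant for replication of the profiles. An article may leave the model-comparison criterion to a fuller document. Most of this stands: an exploratory cross-sectional regression is legitimate, and the gap is a missed opportunity. It does not remove the point, because the article lists its analyses objective by objective and gives Phase 2 a single statistical analysis, which leaves the IPA out.

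Four stronger readings are tempting and are not supported:

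- **Same-visit measurement.** The IPA is completed at home before the neuropsychological assessment. It belongs to the same assessment round, not the same visit.
- **Optimism of 0.06 to 0.08 as the headline.** That assumes scores are picked on the IPA. The study's primary outcome is the CEBA profile, so distinguishing most naturally means separating profiles, which gives 0.02 to 0.03.
- **Model 2 alone is favoured.** Model 1 also rests on profiles estimated in the same sample. The direction of any bias in the comparison has not been shown.
- **The Discussion draws causal conclusions from 1f.** The phrase "potential risk factors for certain CEBA profiles and the corresponding level of societal participation" follows a sentence on demographic and medical predictors of the profiles, which belong to 1e. For participation, that passage speaks only of how profiles relate to it.

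**Conclusion.** The point holds as a worthwhile improvement to 1f. No independent check of the two competing models is described, while an independent sample of 100 with the same measurements is planned. The fact that the retest and Phase 2 IPA enter no stated analysis rests on the article's text alone. The claim that 1f would be judged in its own development sample rests on the natural reading that it uses T0 data.

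The likely inflation of R2 is small, about 0.02 to 0.03, and could reach 0.06 to 0.08 if the scores were chosen on the IPA. Both ranges depend on the assumed number of scores, their correlation and the number selected. A reader might infer that the plan contradicts itself or that its cross-sectional regression is invalid. The documents support neither, since 1f is labelled exploratory and the aim is also worded as a relationship.

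**What to change.** 1. State that both 1f models are fitted on T0 data from the 300 Phase 1 patients, and state how the most distinguishing scores are chosen.
2. Freeze the coefficients and apply both models to the 100 Phase 2 patients. Report out-of-sample R2 with a confidence interval for each, as the measure of prediction and the basis for comparing the models. Analysis 2a already computes profile membership for these patients from the Phase 1 model, so the input for model 1 will exist.
3. Word the Phase 1 result as a concurrent association.
4. Optionally, in the 54 retested patients, regress the T1 IPA on the T0 profile with the T0 IPA as covariate, and report it as an imprecise exploratory estimate with a confidence interval. It should not decide how the Discussion is worded: the sample is small and consists of patients who agreed to be approached again.

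The cost is a little more analysis and probably a slightly less favourable prediction figure. No patients, visits or instruments are added, and because the sample size for 1f is still deferred, the specification can be settled before the analysis.
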